**Specimen collection and testing**

In both groups of tents the study team members will actively search for pilgrims suffering from ILI (defined as subjective or measured fever and at least one respiratory symptom such as cough, sore throat and rhinorrhea) at least once every day. A study team member will collect nasopharyngeal (NP) swab (or throat swab if an NP swab is not doable) for molecular diagnostic testing for respiratory viruses. As a part of the routine care pilgrims in both tent groups will be supplied with generic medications (such as acetaminophen and ibuprofen) for fever or aches in addition to antiviral drugs for confirmed influenza patients.

The swabs will be stored within 2-3 hours at subzero temperature for later molecular diagnostic testing at the Centre for Infectious Diseases and Microbiology Laboratory Services (CIDMLS), Westmead Hospital, NSW, Australia. Pilgrims will provide their email addresses, phone numbers and mail addresses if they wish to receive the results of the laboratory test. Multiplex reverse transcriptase polymerase chain reaction (RT-PCR) for influenza A and B, MRES CoV and other corona viruses, parainfluenza viruses (types 1,2, 3 and 4), RSV A and B, adenoviruses, human metapneumovirus (hMPV), and picorna viruses will be performed. Nasal swabs will be taken for reverse transcriptase polymerase chain reaction (RT-PCR) analysis of respiratory virus infection. The swab used will be Copan nylon flocked dry nasal swab. The study staff who will take the swab will all have been trained to achieve an appropriate sample.

To determine the transmission patterns of influenza viruses among Hajj pilgrims, complete genome sequence of influenza virus will be obtained using a next generation sequencing protocol – using the Illumina MiSeq sequencer available at Westmead Hospital – and which will generate multiple reads per host (~1000X coverage per host; that is, ‘deep’ sequencing). All sequence data generated will be assembled and aligned using the Geneious (http://www.geneious.com) and VICUNA packages,18 with downstream phylogenetic (and other evolutionary) analysis undertaken using the Geneious, Seminator,19 and PhyML packages.20 With these data in hand we will be able to determine; (i) whether the study participants were infected prior or during the Hajj, (ii) whether there was direct viral transmission among the study participants (such that they harbor both ‘majority’ and ‘minority’ genetic variants), and (iii) if direct transmission is established whether this occurs more frequently in the mask versus control groups.

Respiratory samples will not stored or banked for more than it is necessary (eg, to revalidate any result). Any leftover sample will be disposed according to the standard operating procedure of the CIDMLS.

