**Recruitment**

The study will aim to recruit pilgrims at the 2013 Hajj from Saudi Arabia, Qatar and Australia. Whereas in 2014, subjects will also be recruited from Indonesia, Malaysia, Turkey, Morocco, India, Pakistan and Bangladesh (Table 1). Before the commencement of Hajj, the tour groups will be provided with detailed information about the study and encouraged to participate in their respective countries of residence. At Hajj, trained study staff will approach tents for recruitment on the morning or afternoon of the first day of the pilgrim’s stay in Mina (corresponding to13th October, 2013, and 2nd October, 2014). The research team member will explain the study to the assembled pilgrims in each tent and invite them to join the study. If the pilgrims agree to participate, a consent form will be signed and a baseline questionnaire will be filled which will include collecting relevant demographics, vaccination history and clinical information such as respiratory symptoms with duration and pre-existing medical condition (Appendix 1). The participants will be informed whether their tent has been randomised to facemask wearing or no facemask wearing.

­

13th

October

Pilgrims settle into tents

Randomisation

Intervention tents Control tents

All fill baseline questionnaires

Given *Hajj diaries*

Receive masks and demonstration. Do not receive masks

Start wearing masks

14th October

All record symptoms in Hajj diaries

Symptomatic pilgrims are swabbed

Continue mask wearing Do not wear masks

15th October

16th October

Study staff collect *Hajj diaries* in the evening

17th October

18th October

Evening

19th October

Evening

Pilgrims leave Mina and start keeping *post-Hajj* diaries

20th October

No need to keep *post-Hajj* diaries

Mask wearing is no more required No need to avoid mask wearing

Nasal swabs get transported to Sydney

Pilgrims send *post-Hajj* diaries to research physicians

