**Figure 2: Key steps of the study at the Hajj 2013**

**Inclusion criteria**
Pilgrims from participating countries staying in their respective tents
Age ≥18 years.
Informed consent has been agreed and signed.

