**Exclusion criteria**
Children aged less than 18 years.
Participation in another clinical trial investigating a medical intervention that may interfere with study outcome measures like proven viral RTI.
Known contraindication to mask use (eg, allergy to surgical mask materials).

Refused to sign a consent form.

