**Data collection**

For the tents assigned to mask use, 25 masks will be provided to each participant, one to be worn continuously (24/7), and then replaced every few hours (sooner if wet), for the 5 days at Mina.

The mask for this study is ‘3M™ Standard Tie-On Surgical Mask, Cat No: 1816’. Masks may be removed for eating, praying, washing, brushing teeth, or if the pilgrim experiences discomfort. Oral and written information about the instructions for correct mask wearing and disposal will be provided to the mask group (Appendix 2). Study staff will practically demonstrate the correct method of how to wear masks and help pilgrims to put on their mask for the first time. Masks can be changed every 4- 6 hours or more frequently if the masks become damp or damaged. Handouts will be distributed to all pilgrims at ‘mask tents’ to encourage correct mask wearing and explain the correct disposal of used masks. Small plastic bags will be provided for mask disposal and subjects will be instructed to discard the plastic bag containing used masks into waste bins provided for subsequent sanitary disposal. A subset of disused masks can be saved for further testing by multiplex viral PCR. A research team member will be available each morning and evening to distribute additional facemasks should pilgrims request extra, and to document any reported ILI symptoms development.

On recruitment, study staff will record each tent number, the number of people recruited and the total number of people in the tent. All pilgrims will be given a *Hajj health* diary (Appendix 3) for 5 nights at Mina (corresponding to 13-17 October, 2013, and 2-6 October, 2014). Each diary will have a unique barcode identifying the diaries with a specific study participant. The diaries will contain questions on demographics, medical conditions, and influenza vaccination history (Appendices 3 and 4). Each participant will provide information about the presence or absence of respiratory symptoms and fever in the diary every day whenever it is most convenient (eg after their evening meal). Pilgrims will also record in their diaries the amount of time they have worn the mask, the number of masks used per day and whether they were wearing one in their sleep.

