**Sample size calculation**

Assuming that the prevalence of symptomatic RTIs is 30% in the controls and the prevalence of laboratory-proven respiratory viral infection in controls is approximately 12% the intervention could be considered clinically worthwhile if it can reduce the prevalence of syndromic or proven viral RTI by 50%.21,22

Assuming a moderate intra-cluster correlation of 10% and a mean of 75 participants per cluster (tent), and inflating the sample by a factor of 8.4 to account for clustering, the sample size required for a cRCT to detect a reduction from 12% to 6% with 80% power at 5% significance is 2976 per arm. An additional inflation factor of 1.18 will allow for up to 15% loss to follow-up or incomplete outcome data. This results in a sample size of approximately 3500 participants per treatment making a total of 7000.

For the first primary outcome (clinical/syndromic RTIs) a smaller sample would be sufficient to answer a more generic question, namely prevention of symptomatic RTI. The sample size required for detecting a reduction from 30% prevalence of RTIs to 15% with 80% power at 5% significance and considering for clustering and loss to follow-up is about 1170 participants per treatment making a total of 2340.

| **Countries** | **Total number of pilgrims** | **Number of recruits** | |
| --- | --- | --- | --- |
| **2013** | **2014** |
| Saudi Arabia | 1,000,000 | 2,200 | 2,200 |
| Indonesia | 200,000 |  | 500 |
| India | 170,000 |  | 450 |
| Pakistan | 150,000 |  | 350 |
| Turkey | 120,000 |  | 300 |
| Bangladesh | 65,000 |  | 200 |
| Morocco | 32,000 |  | 100 |
| Malaysia | 28,000 |  | 100 |
| Australia | 5,000 | 200 | 200 |
| Qatar | 2,000 | 100 | 100 |
| Total | 1,770,000 | 2500 | 4500 |

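### Illness that began before the first mask can count as a primary event: neither eligibility nor the case definition requires onset after enrolment

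*Protocol*

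**What the plan says.** - **Eligibility.** The Inclusion criteria admit "Pilgrims from participating countries staying in their respective tents" who are adult and consent. The Exclusion criteria list age under 18, participation in an interfering trial, refusal of consent, and "Known contraindication to mask use (eg, allergy to surgical mask materials"). Current respiratory illness is not listed.
- **Timing.** Under Recruitment, "trained study staff will approach tents for recruitment on the morning or afternoon of the first day of the pilgrim’s stay in Mina". Masks are handed out then and worn "for the 5 days at Mina" (Data collection).
- **Baseline record.** The questionnaire collects "clinical information such as respiratory symptoms with duration and pre-existing medical condition" (Recruitment). No section uses that item for eligibility, case definition or analysis.
- **Case finding.** "In both groups of tents the study team members will actively search for pilgrims suffering from ILI", at least daily, and those found are swabbed (Specimen collection and testing). ILI is defined there by fever plus a respiratory symptom, with no reference to when it began.
- **Analysis.** Data analysis names ILI and laboratory-confirmed virus as the primary endpoints, by intention to treat, with no rule for illness present at baseline.
- **Sample size.** "the intervention could be considered clinically worthwhile if it can reduce the prevalence of syndromic or proven viral RTI by 50"%. The control rates, 30% and 12%, are also given as prevalences.
- **Pre-Hajj infection.** Sequencing is to show "whether the study participants were infected prior or during the Hajj". This covers influenza only, serves the secondary transmission aim, and is not tied to the primary count.

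**The concern.** Design of the trial states the purpose as prevention. A mask first worn on day one in Mina cannot prevent an illness that began earlier. A pilgrim who arrives febrile and coughing meets the ILI definition at the first search, is swabbed and, if positive, becomes a primary event in either arm. Such cases are balanced between arms in expectation and do not respond to the intervention. They add the same amount to both event rates, which moves the risk ratio towards 1 and costs power. An effective mask could then look less effective than it is, or the comparison could miss significance.

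**Working it through.** **Inputs from the protocol (Sample size calculation).** Control rate 12% and mask rate 6% for proven infection; 30% and 15% for symptomatic RTI; 80% power; 5% significance (taken as two-sided); intra-cluster correlation 0.10; 75 participants per tent; 2976 evaluable per arm; inflation 1.18 for losses.

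**Input not in the protocol.** q, the share of the control rate that is pre-mask illness. It is an assumption, shown as a range.

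**Step 1. Reproduce the plan's figures.** The design effect is 1 + 74 × 0.10 = 8.4. For 12% against 6%, the pooled-variance formula gives 356 per arm, and 356 × 8.4 = 2990. The unpooled formula gives 353.2, and 353.2 × 8.4 = 2967. The stated 2976 lies between them, and 2976 × 1.18 = 3512, stated as about 3500. For 30% against 15%, unpooled, 118 × 8.4 × 1.18 = 1170, as stated. The arithmetic is sound and is not in dispute.

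**Step 2. Pre-mask cases inside the 12%.** Effective n per arm is 2976 / 8.4 = 354.3. With a true halving of preventable illness:

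- mask-arm rate p2 = 0.12q + 0.06(1 − q)
- observed RR = p2 / 0.12 = 0.5 + 0.5q
- power = Φ[(d − 1.96·se0) / se1], where d = p1 − p2, se0 = √(2p̄(1 − p̄)/n), se1 = √((p1(1 − p1) + p2(1 − p2))/n)

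Example, q = 20%: p2 = 0.024 + 0.048 = 0.072; d = 0.048; p̄ = 0.096; se0 = 0.02213; se1 = 0.02206; (0.048 − 0.04338)/0.02206 = 0.209; Φ = 0.58.

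| q (assumed) | Mask-arm rate | Observed RR | Power |
|---|---|---|---|
| 0 | 6.0% | 0.50 | 80% |
| 10% | 6.6% | 0.55 | 70% |
| 20% | 7.2% | 0.60 | 58% |
| 30% | 7.8% | 0.65 | 46% |

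The syndromic outcome behaves alike. With 1170 / 1.18 / 8.4 = 118.0 effective per arm, power is 79%, 69%, 58% and 46% for the same q.

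**Step 3. Pre-mask cases on top of the 12% and 6%.** If a proportion x of participants is already ill, the rates are x + (1 − x) × 0.12 and x + (1 − x) × 0.06.

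| x (assumed) | Control | Mask | RR | Risk difference | Power |
|---|---|---|---|---|---|
| 1% | 12.9% | 6.9% | 0.54 | 5.9 points | 75% |
| 2% | 13.8% | 7.9% | 0.57 | 5.9 points | 71% |
| 3% | 14.6% | 8.8% | 0.60 | 5.8 points | 67% |

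The risk difference is 6.0 points without such cases, so it barely changes. The risk ratio and power do.

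**Step 4. What an onset rule recovers.** A baseline symptom record finds illness already apparent, not infection still incubating. Suppose the rule removes half of q (an assumption). The control rate becomes 0.12(1 − q/2) and the mask rate 0.06(1 − q) + 0.12 × q/2, which is 6.0% at every q.

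| q | Control | Mask | RR | Power with rule | Power without |
|---|---|---|---|---|---|
| 10% | 11.4% | 6.0% | 0.53 | 72% | 70% |
| 20% | 10.8% | 6.0% | 0.56 | 63% | 58% |
| 30% | 10.2% | 6.0% | 0.59 | 54% | 46% |

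The estimate moves back towards 0.50 and power rises, although fewer events are counted.

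**The case against.** The strongest reply is that the protocol is silent here rather than wrong. Handling of baseline-symptomatic participants and the onset window are often set in an SAP, which is not at hand. The protocol collects what such a rule needs: baseline symptoms with duration, and daily diaries. Its stated aim is prevention, and Data collection has staff note ILI symptoms as they develop, which suggests new illness. The word prevalence comes from the sample size text, not from the endpoint statement.

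Part of this stands: the intention may well be to count new illness, and an SAP could say so. But eligibility and the case definition are protocol matters. This protocol does fix them, and does so without onset. Staff following it would swab and count illness present on arrival.

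Three further objections stand and limit the point:

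- **Size.** The documents give no share of illness present at enrolment. A reader might infer from the five-day stay that early cases are a large part of the total; nothing in the protocol establishes that. For ILI, the post-Hajj diaries also extend follow-up beyond Mina, so the short-stay argument bears mainly on the swabbed endpoint.
- **Benefit of the fix.** A reader might infer that counting new onsets restores a risk ratio of 0.50. It does not, because infections incubating at enrolment with later onset still count.
- **Risk of the fix.** Figure 2 places randomisation before the baseline questionnaire, and participants are told their allocation. Removing people on a self-report given after disclosure could differ by arm. The order of recording has to be fixed as well.

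**Conclusion.** The point holds. As written, the plan counts illness that preceded any mask, and the expected direction is towards no effect on the ratio scale, whatever the share. The amount is unknown. Under the assumed shares of 10% to 30% of the control rate, a true risk ratio of 0.50 appears as 0.55 to 0.65, and power falls from 80% to between 70% and 46%. If the cases are instead additional (1% to 3% of participants), the risk ratio is 0.54 to 0.60, power is 75% to 67%, and the risk difference is almost unchanged.

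These figures take the protocol's design effect and evaluable numbers as given and assume pre-mask illness is balanced. Balance is expected but not assured: whole tents are allocated, about 40 per arm evaluable (2976 / 75), so a chance imbalance could shift a single trial's result either way. The documents do not support the stronger conclusion that the reported effect would necessarily be much smaller than the true one; at a 10% share it is 0.55 against 0.50.

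**What to change.** 1. Define both primary events, ILI and laboratory-confirmed infection, as illness with onset after enrolment.
2. Keep pilgrims with symptoms on the baseline questionnaire enrolled and in their allocated arm, but outside the at-risk set (numerator and denominator), by the same rule in both arms.
3. Require the baseline symptom record to be complete before the tent's allocation is disclosed, and bring Figure 2 into line.
4. State the 12% and 30% as rates of new illness, or revise them if they are not.
5. As sensitivity analyses, report the all-cases intention-to-treat result and one that drops onsets in the first day or so. No lag has a source in the documents, so it should not define the primary event.

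**Cost.** A few sentences of definition and no new data. The order of recording is a field procedure that must be settled before recruitment, because it cannot be repaired afterwards. Somewhat fewer events are counted, and incubating infections leave some dilution in place.

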**Follow up**

All participants will be followed up (e.g. by telephone, mails, emails) by study physicians in their country of residence to collect their *post-Hajj health* diaries (as well as *Hajj health* dairies if not collected earlier). Having obtained prior consent from the participants to do so, their GPs/family physicians (if available) may be contacted to validate any clinical detail, especially to verify vaccination histories.

**Data analysis**

Data available from questionnaires, diaries and laboratory tests will be analysed anonymously to examine whether mask use makes a significant difference in reducing the frequency of laboratory-confirmed respiratory virus infection (including influenza, corona virus or other respiratory viruses). The primary endpoints (effectiveness and efficacy of facemasks against ILI and laboratory-confirmed viruses respectively) will be analysed by intention to treat.

The self-reported uptake rates of influenza vaccination will be determined and vaccine effectiveness will be estimated based on the case-negative case-control methodology.

The results from the genomic sequencing of influenza virus will assist us understanding the genetic relatedness of circulating influenza strains at Hajj and the transmission pattern of influenza among pilgrims.

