**Objectives**

*Primary aim*

1. To evaluate the efficacy of facemasks against laboratory-confirmed respiratory viral infections (including influenza, MERS CoV and other respiratory viruses) at Hajj 2013 and 2014.

*Secondary aims*

1. To investigate the transmission pattern of influenza virus at Hajj by studying the genetic relatedness between circulating influenza viruses using deep genomic sequencing.
2. To determine the self-reported influenza vaccine uptake and evaluate its effectiveness at Hajj using a test-negative case-control design.

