**Table 1: Proposed number of pilgrims from each participating country**

To achieve the full sample size we aim to conduct the study over two years (2013 and 2014). About 2500 pilgrims (or at least 2340) will be recruited in 2013 which will give an answer for the RTI outcome and could build on that sample for the second outcome (proven infection) which ultimately will be completed by recruiting another 4500 pilgrims in 2014. Proportionate (or balanced) number of pilgrims will be recruited from each participating country according to the number of pilgrims attending Hajj from these countries (see Table 1).

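### The protocol disagrees with itself on the primary endpoint and sizes two outcomes at a full 5% each; if either may carry the claim, two-sided error is about 9–10%

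*Protocol*

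**What the plan says.** The relevant parts of the protocol, side by side:

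- **Objectives.** The only primary aim is "To evaluate the efficacy of facemasks against laboratory-confirmed respiratory viral infections". The two secondary aims concern influenza transmission and vaccine uptake and effectiveness. Influenza-like illness (ILI) and syndromic RTI appear under no aim.
- **Data analysis.** There are two primary endpoints: "The primary endpoints (effectiveness and efficacy of facemasks against ILI and laboratory-confirmed viruses respectively) will be analysed by intention to treat".
- **Sample size calculation, benefit sought.** Masks are held to be "clinically worthwhile if it can reduce the prevalence of syndromic or proven viral RTI by 50" per cent.
- **Sample size calculation, laboratory outcome.** The size needed "to detect a reduction from 12% to 6% with 80% power at 5% significance is 2976 per arm", which becomes about 3500 per arm after allowance for loss.
- **Sample size calculation, syndromic outcome.** "For the first primary outcome (clinical/syndromic RTIs) a smaller sample would be sufficient to answer a more generic question". It is sized for 30% against 15%, again at 80% power and 5% significance, giving about 1170 per arm or 2340 in total.
- **Text after Table 1.** "About 2500 pilgrims (or at least 2340) will be recruited in 2013 which will give an answer for the RTI outcome". Proven infection is called the second outcome and is completed with 4500 more recruits in 2014.

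The name of the syndromic endpoint also changes. Data analysis says ILI, which Specimen collection and testing defines as fever, felt or measured, plus one or more respiratory symptoms. The sample size text says symptomatic, clinical or syndromic RTI and states no fever requirement.

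Nothing in the protocol divides the 5% between the outcomes, orders the tests, or requires success on both.

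**The concern.** Under the Objectives the laboratory result decides the trial. Under Data analysis the two results share that role. Under the Sample size calculation the syndromic result comes first. With two outcomes each given a full 5%, and worth described as an effect on one or the other, the trial appears to have two chances of a positive finding.

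This matters most for a split result. The Background reports that pooled earlier trials favoured masks on ILI but showed no protection against laboratory-proven influenza. If this trial gives the same pattern, the protocol supports both a positive and a negative reading.

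The syndromic outcome is also the more exposed to bias. Participants are told their tent's allocation (Recruitment) and record their own symptoms in diaries (Data collection). The laboratory outcome is not free of this, because swabs are taken from people found to have ILI, but it also needs a positive PCR.

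**Working it through.** **1. Reproduce the plan's sample sizes.** Inputs from the Sample size calculation: 12% against 6%; 30% against 15%; 80% power; 5% significance (sidedness not stated); intra-cluster correlation 0.10; 75 per tent; 15% loss.

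Design effect: 1 + (75 − 1) × 0.10 = 8.4, as stated.

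Per arm before clustering, two-sided: n = [1.96 √(2p̄(1 − p̄)) + 0.8416 √(p₁(1 − p₁) + p₂(1 − p₂))]² / (p₁ − p₂)².

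- Laboratory, p̄ = 0.09: [1.96 √0.1638 + 0.8416 √0.1620]² / 0.0036 gives 356. 356 × 8.4 = 2990. With unpooled variance, 353.2 × 8.4 = 2967. Stated: 2976. Then 2976 / 0.85 = 3501.
- RTI, p̄ = 0.225: [1.96 √0.34875 + 0.8416 √0.3375]² / 0.0225 gives 121. 121 × 8.4 / 0.85 = 1196. With unpooled variance, 1163. Stated: about 1170.

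One-sided versions give 2360 and 939. Two-sided versions with continuity correction give 3268 and 1324. Neither pair matches. Each outcome was therefore sized at a full two-sided 5%, with no split.

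**2. Correlation between the two tests.** The protocol gives no correlation, so this is an assumption. If every laboratory-proven case is also an RTI case, the control-arm rates give φ = √(0.12 × 0.70 / (0.30 × 0.88)) = 0.56. If RTI is tested on 2013 recruits only and the laboratory outcome on all 7000, multiply by √(2500/7000) = 0.60, which gives 0.34.

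**3. Chance of at least one false positive, each test at |z| > 1.96.**

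| Tests | Correlation | Two-sided | Benefit only |
| --- | --- | --- | --- |
| Two, independent | 0 | 1 − 0.95² = 9.75% | 1 − 0.975² = 4.9% |
| RTI on 2013, laboratory on all | 0.34 | 9.45% | 4.7% |
| Both on all 7000 | 0.56 | 8.85% | 4.4% |

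The correlated rows come from simulated normal test statistics. Two 5% tests cannot exceed 10% whatever the correlation. A higher correlation lowers the rate, for example to 7.9% at 0.8, but 0.56 is already the value with full overlap of cases at the protocol's rates.

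**4. An added assumption: RTI re-tested on all 7000.** With three tests (RTI on 2013, RTI on all, laboratory on all) the two-sided rate is 12.4% at φ = 0.56 and 13.3% at φ = 0.

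**5. Effect of splitting 5% as 2.5% each.** With the planned numbers, power falls to 71% for the laboratory outcome (2976 per arm analysed) and to 70–73% for RTI (1170–1250 per arm recruited). Restoring 80% needs 432 × 8.4 / 0.85 ≈ 4270 per arm for the laboratory outcome and 147 × 8.4 / 0.85 ≈ 1453 for RTI.

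**6. Effect of a fixed sequence, laboratory first.** The laboratory test keeps 5% and its 80% power. RTI on the full sample has an effective 2976 / 8.4 = 354 per arm, and on its own exceeds 99% power for 30% against 15%. RTI can be claimed only after laboratory success, however, so the probability of an RTI claim cannot exceed about 80%.

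**The case against.** The strongest reply is that the protocol never states an either/or decision rule. The sentence on syndromic or proven RTI concerns clinical worth and introduces both sample size calculations. Data analysis separates effectiveness against ILI from efficacy against laboratory-confirmed viruses, and the sample size text calls RTI the more generic question. One can read this as two questions, reported separately, in which case a joint error rate need not apply. Testing order and multiplicity are also commonly left to a statistical analysis plan, which is not at hand.

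Much of this stands: the error rate is conditional on a claim structure that has to be inferred. But an analysis plan cannot make the Objectives agree with Data analysis and the Sample size calculation. Nor can it divide the 5% later without breaking the stated 80% power.

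Four stronger readings are tempting and are not supported:

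- **Error of 12–13%.** This needs a third test. The text after Table 1 ties RTI to the 2013 recruits and the 2014 recruits to proven infection.
- **An interim look.** About 2500, or at least 2340, is the complete planned sample for RTI. The timing adds no error of its own. No text says that a between-arm result would be released before 2014, so an effect on later behaviour or recruitment is speculation.
- **A 9–10% chance of wrongly claiming that masks work.** That figure includes false findings of harm; for benefit alone it is 4.4–4.9% against 2.5%.
- **A laboratory endpoint free of reporting bias.** It passes through the same unblinded symptom search.

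**Conclusion.** The concern holds in a limited form. The contradiction over the primary endpoint is in the text and needs no assumption. That each outcome was sized at a full two-sided 5% follows from reproducing the numbers, to within 0.5% for the laboratory outcome and 3% for RTI.

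The size of the error rests on two assumptions: that either result alone may carry the claim, and that the two test statistics have a correlation between 0 and 0.56. It is then about 9–10%, roughly double the nominal level on either the two-sided or the benefit-only scale. The source is having two endpoints, not when RTI is read out.

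**What to change.** Amend the Objectives, Data analysis, Sample size calculation and the text after Table 1 so that they agree:

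- Make laboratory-confirmed infection the single primary endpoint, tested once at two-sided 5% after the 2014 data are complete. This matches the existing primary aim and the total of 7000.
- Give the syndromic endpoint one name and one definition, ILI or RTI, throughout. Test it second, on the full sample, and only if the first test is significant.
- Reword the clinical-worth sentence and the statement about a 2013 RTI answer to match.

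This needs no extra participants and leaves laboratory power at 80%. The cost is that no confirmatory RTI claim can be made after 2013, and a later one depends on laboratory success. A true RTI benefit would go unclaimed whenever the laboratory test fails.

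If the sponsor wants two primary endpoints or a confirmatory RTI answer from 2013, the alternative is an explicit division of the 5% with both powers restated. At 2.5% each they are about 71% with the planned numbers. Keeping 80% would need about 2 × 4270 = 8540 participants for the laboratory outcome and 2 × 1453 = 2906 for RTI.
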